#### Control Variables (Time-Constant/Baseline):

1. *Socio-demographics* will include age, gender, self-reported race and ethnicity, country of origin, income, highest level of education, employment status, global health status, and insurance.
2. *Diabetes and Medical History* will include time since diabetes diagnosis, receipt of diabetes education, current therapy, diabetes complications, and co-morbid conditions.

3. *Health Literacy* will be assessed using three screening questions with high discriminatory power among English and Spanish speaking populations.
4. *Mobile phone use* and comfort sending text messages will also be assessed using five items.
5. *Environmental Surveys* that assess loneliness, social cohesion, and neighborhood safety will be administered.

Additional Control Variable for mDAS sub-study

6. *Medication History* will include reported pain medications, sleep aids, or psychotropic medications prescribed and/or taken.

Intermediate Variables (Time-Varying): Intermediate variables will be collected at five time points (0, 6-, 12-, 18-, and 24-months).

1. *Perceived severity* of diabetes and *perceived susceptibility* will be assessed through two items adapted from Bradley.
2. *Perceived benefits of therapy* will be measured by the five-item survey related to benefits of therapy.
3. *Depression* will be measured using the nine-item Patient Health Questionnaire (PHQ-9).
4. *Social Support* will be measured using an assessment of amount of total support received and satisfaction of support from family, friends and healthcare team.
5. *Self-efficacy* will be measured by the Stanford 8-item self-efficacy for diabetes survey.

Process Measures:

1. *HC Activity* will be collected on a standardized worksheet completed after every participant contact (by phone and in-person). Information will include mode, time, and content of contact, results of glucose or blood pressure self-monitoring, goals, life events, pharmacist interactions, and interventions. [name] will review HC worksheets for intervention fidelity.
2. *Text Messaging:* Detailed information on text messages sent and received are stored in a *mytapp* database. Drs. [name] and [name] will login to *mytapp* to review message data monthly to ensure fidelity. Additionally, [name] will login to *mytapp* to review message data from the sub-study weekly.
3. *PCP and Pharmacist Activity:* The pharmacist will reconcile medications as part of the intervention, and the reconciled list from the medical chart will be used as data

to evaluate medication changes and overall complexity of therapy. Intensification of therapy will be defined as the number of increases in the dosage of antihypertensive, hypoglycemic agent, or insulin or the addition of a new agent since the baseline visit. Chart review will define the number of PCP visits and pharmacist videoconferences as well as the number of pharmacist- or physician-initiated medication changes.

4. *Patient Summary Evaluation*: Feedback will be collected from participants regarding their experience with the health coach, pharmacist, and videoconference technology. Individual responses will not be shared directly with the participant's health coach or pharmacist. Evaluation will be collected at 12 months for participants who receive the intervention in Year 1 or 24 months for those who receive it in Year 2.

Physiologic Outcomes and Quality of Life: Physiologic outcomes will be collected at five time points (0, 6-, 12-, 18-, and 24-months). CIC research staff will perform phlebotomy, blood pressure, weight and height recordings while being blinded to subject group assignment.

1. *Hemoglobin A1c and fasting lipid profile* (total cholesterol, HDL, LDL, and triglycerides) will be obtained via phlebotomy. The A1c laboratory test has National Glycohemoglobin Standardization Program certification.
2. A calibrated digital scale will measure *weight*.
3. At baseline, a height stadiometer will measure body *height*, with subjects removing their shoes (for BMI assessment).
4. *Blood pressure* will be assessed on subjects sitting down for at least five minutes, following standard procedure. Extreme blood pressures are reported to [name] per CIC protocol.
5. *Health Related Quality of Life* will be measured using the EQ5-D (general) and DDS4 (diabetes specific).

Medication Adherence and Behavioral Outcomes: Medication adherence will be assessed using self-report and objective measures.

1. A self-report *medication adherence* survey will be included for all diabetes medications (developed by Lu et al, AIDS Behav 2008; Gonzalez JS et al, Diabetes Care, 2013). This instrument includes three items.
2. *Pharmacy fill data* will provide a more valuable method of adherence evaluation. Each participant will provide contact information for all pharmacies where prescriptions have been filled for the past two years. A signed HIPAA authorization form allows research personnel to contact pharmacies for medication fill information. For each prescription, the medication name, date dispensed, dosage,

- frequency, quantity, and supply will be requested. The Proportion of Days Covered (PDC) will be calculated for all diabetes, hypertension, and hyperlipidemia medications.
3. The revised *Summary of Diabetes Self-Care Activities Measure (SDSCA)* will capture basic diet, exercise, blood sugar testing, foot care, and smoking with 11 core items.
  4. *Alcohol misuse* will be assessed with the AUDIT-C brief screen. This instrument defines those with heavy/hazardous drinking behaviors.

Cost and Healthcare Utilization Data: We will conduct a cost-utility analysis comparing *mDAS* with usual care, following the guidelines for conducting pharmacoeconomic analyses by the Panel on Cost-Effectiveness and Medicine and the International Society for Pharmacoeconomics and Outcomes Research. We will conduct the analysis from the health-system perspective, and include the costs of running the program as well as the costs associated with patient health services utilization. Costs will include pharmacists and HCs (training and implementation), educational materials, tablet computers with data service, text messaging, and videoconferencing. Health services utilization will include costs associated with hospital admissions, emergency room visits, outpatient visits and prescription medications during the intervention period. Participants will be followed throughout the study to obtain data on their programmatic and healthcare services related costs. At data collection points, research assistants will obtain the necessary information from patients on healthcare use outside of UI Health. We will capture UI Health care information electronically from the hospital electronic records and billing data for enrolled subjects. We have previously analyzed similar UI Health data. Additional costs (salaries for HCs, etc.) will be estimated from prevailing internal costs at the time. Cost estimations for healthcare use will be based on national Medicare reimbursement rates (average DRG rates) for hospitalization, Medicare fee schedules for physician and other professional services, and Medicare's Resource-Based Relative Value Scale for outpatient procedures. Since our study will span a period exceeding one year, appropriate costs will be discounted and adjusted for inflation.

Data Management: We utilize REDCap (Vanderbilt University) for data entry. Our data manager is experienced in form creation, export, and randomization functions. Data will be exported, cleaned, and analyzed in SPSS, SAS, or R. To address missing data, we will examine the data for patterns of missingness and potential bias in missingness (SPSS Missing Values). If data are not missing at random, we will apply one of several available imputation methods in a sensitivity analysis based on the nature and extent of missing data. We will determine effectiveness using intention-to-treat principles with actual imputation of missing data. This will allow us to appreciate the potential biases inherent in a "real-world" setting due to drop out and poor adherence to study procedures.

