### **Transition and Retention**

Despite having "access" to healthcare, participants will be economically vulnerable individuals with uncontrolled diabetes. Ethically, we acknowledge that the "usual care" currently received often does not meet patients' needs or standards of care. Therefore, participants assigned to usual care will receive initial support to engage existing resources available through UI Health, such that healthcare providers will consider this an acceptable alternative upon randomization (clinical equipoise).

Upon randomization, participants will receive referrals to a diabetes educator and clinical pharmacist for medication reconciliation, adherence support, and education. Staff can schedule the visit at data collection. This is important as our prior work with medication reconciliation identified discrepancies in almost 60% of patients. A one-page list of clinic resources with names and direct telephone numbers (e.g., social worker) will be provided so they can more easily navigate the system. Finally, low-literacy, paper-based diabetes education information will be provided. At the end of year 1, these patients will cross-over and receive *mDAS*. Prior to this transition, HCs will work with the patients and their social support network to prepare them for the transition. Participants randomized to usual care will receive *mDAS* for one year.

*Retention strategies.* Participants will be reimbursed \$30 for each data collection. Participants assigned to the intervention in year one will receive an additional \$50 at 6 months and 12 months if they complete at least one videoconference before each data collection. Participants assigned to the intervention in year two will receive an additional \$50 at 18 months and 24 months if they complete at least one videoconference before each data collection. Participants who complete all five data collection visits and videoconferences with the pharmacist as described above will receive up to \$250 for completing the study.

*Additional Retention Strategies for mDAS Sleep Sub-study Supplement* Participants will be reimbursed an additional \$40 for participating in the sleep sub-study and turning in the wrist actigraph.

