If the intervention is effective, we will examine whether changes in self-efficacy, health beliefs, or social support serve as mediators for improved outcomes according to our conceptual framework. In addition, we will explore diabetes-related behaviors as well as medication treatment intensification as mediators using MPlus. To further identify the relative contributions of videoconferencing and/or text messaging, we will conduct mediational modeling with videoconferencing time, number of text messages, and HC contact time as mediating variables. This may describe any dose-response relationships between mHealth utilization and outcomes. We will compute bias-corrected bootstrap standard errors using MPlus. This offers accurate confidence intervals for mediation coefficients. Due to anticipated relationships between HC activity level and mHealth delivery, we plan to inspect correlations between mediators and incorporate any significant findings in model development. This analysis will demonstrate whether intervention effects are sensitive to mediators. Finally, given the sample size, observed (rather than latent) variables will be used in the mediation models. To enhance the power of mediation modeling, we will adopt an  $\alpha=.10$  Type I error criterion to improve the chances of finding promising mediators for future study.

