### **PROCEDURES**

#### **A. Appointment Scheduling**

- 1. New patients will be scheduled for an initial videoconference with pharmacist after health coach (HC) has completed at least one home visit with patient.
- 2. The HC will schedule the initial telehealth pharmacy visit within 90 days of a patient's enrollment in the study. Initial visits will be scheduled for 60 minutes. Scheduling will be done according to each recruitment site's preference.
  - a. Medication Therapy Management Clinic (MTMC): Visits will be scheduled in the electronic Medication Management Therapy Clinic (MTMC) appointment book in Cerner.

For instructions on scheduling, please refer to the MTMC Scheduling Guide (Appendix A). Appointment times will be based on patient room availability as well as the patient's and HC's availability. Only one research telehealth patient visit may be scheduled per half day (between the hours of 9am-12pm and 1pm – 4 pm. The pharmacist assigned to the patient at their initial visit will continue to see them for the duration of their time in the study, when possible.

- b. Mile Square: HC will forward a clinic note to the pharmacist with a message requesting an appointment. The HC will also text the pharmacist to alert them that a telehealth visit is needed. The pharmacist will work with the HC to find an agreeable time and will have that time blocked in the appointment book in Cerner.
  - c. Family Medicine (University Village) – HCs will schedule appointments directly with IRB approved pharmacists via encrypted email (preferred) or phone. Pharmacists will keep a separate calendar and block the time in their Cerner appointment book.
- 3. Subsequent visits will be scheduled by the pharmacist at each telehealth visit, based on the needs of the patient, as well as the availability of the patient and HC. These visits will be scheduled for a minimum of 30 minutes. However, visits with Spanish-speaking patients should be scheduled for 60 minutes to allow for translation.
- 4. Encounter cancellations will be made as soon as possible (*at least 24 hours prior to scheduled time*) when possible. The HC will call or text the patient the day before to confirm the visit. HCs may reschedule visits at the patient's request, but must work with the pharmacist to ensure their availability.

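### Intensification and regimen complexity are tied to a medication list that mDAS itself creates after baseline, so list corrections could be counted as intensification more often in mDAS than in Year 1 usual care

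*Protocol*

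**What the plan says.** Section 8.0, Process Measures, item 3 names the data source: "The pharmacist will reconcile medications as part of the intervention, and the reconciled list from the medical chart will be used as data". The sentence continues with the purpose and runs into the definition: "to evaluate medication changes and overall complexity of therapy. Intensification of therapy will be defined as the number of increases in the dosage". In full, the count covers blood pressure drugs, glucose-lowering drugs and insulin, "or the addition of a new agent since the baseline visit". The sentence with the definition names no source of its own.

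The same item, and Section 6.1 (Evaluation of Pharmacist Activity and Medication Changes), also plan a research-assistant chart review that counts medication changes started by a pharmacist or a physician. It is not limited to one arm. The protocol does not say whether this review or the reconciled list supplies the intensification count.

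On timing, the Pharmacy Management Protocol (A. Appointment Scheduling) says: "The HC will schedule the initial telehealth pharmacy visit within 90 days of a patient's enrollment in the study". Section 6.4 places reconciliation at that first encounter, and Section 6.0 places allocation after consent and baseline data collection.

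On how often reconciliation alters a list, Transition and Retention reports that "our prior work with medication reconciliation identified discrepancies in almost 60% of patients".

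On use, Section 12.0 (Primary Outcomes) says that, if the intervention is effective, "we will explore diabetes-related behaviors as well as medication treatment intensification as mediators using MPlus".

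**The concern.** A measure meant to explain how mDAS works should be recorded in the same way in both arms. Here the named record is a product of mDAS. When a pharmacist reconciles a list, a drug the patient already took may be added, or a recorded dose corrected upward. Compared with an unreconciled baseline, either entry can look like a new agent or a dose increase although nobody prescribed anything. If reconciliation is more common in mDAS, such entries accumulate there.

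At stake is the arm comparison of intensification and of regimen complexity, and with it the mediation analysis. Section 12.0 also plans to look at BMI and quality of life as consequences of intensification, but does not say that this count is used for that purpose.

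**Working it through.** The protocol states no figure for this measure, so there is none to reproduce. The check compares the passages and then illustrates the size.

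**Step 1: does the reconciled list exist at baseline?** The protocol specifies none for either arm. It first arises at the first pharmacist encounter, after randomisation. Section 4.2 excludes patients with regular pharmacist support, so most baseline chart lists are probably unreconciled; that is an inference. Section 8.0 does record current therapy at baseline in both arms, without stating how.

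**Step 2: is it equally available in both arms in Year 1?** In mDAS, medications are reviewed and updated at each encounter (Pharmacy Management Protocol, E. Patient Records). Usual care receives a referral that staff may book (Transition and Retention), which the Usual Care Component reduces to contact information. Section 6.0 describes the service as under-used. No uptake rate is given.

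**Step 3: is a correction separated from a prescribed change?** The intensification definition has no such rule. The chart review could make the separation, but it is not tied to the definition.

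**Step 4: illustration of size.**

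- From the protocol: discrepancy rate 0.60; evaluable patients 220 × 0.80 = 176, or 88 per arm if allocation is equal.
- Assumed: q, the share of patients with a discrepancy whose correction resembles a new agent or a higher dose; uT and uC, the shares reconciled in Year 1 in mDAS and usual care; a true rate of any intensification of 30% in both arms, independent of corrections.

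Spurious excess per patient = 0.60 × q × (uT − uC). For q = 0.25, uT = 0.8, uC = 0.2: 0.60 × 0.25 × 0.6 = 0.09.

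For any intensification, the recorded proportion in an arm with uptake u is 1 − (1 − 0.30)(1 − 0.60 × q × u). In the same case:

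- mDAS: 1 − 0.70 × 0.88 = 0.384
- usual care: 1 − 0.70 × 0.97 = 0.321

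The last column is the chance that a two-sided 5% comparison of two proportions shows a significant excess in mDAS; it would be 2.5% without the artefact.

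| q | uT, uC | Excess per patient | Recorded mDAS vs usual care | Chance of false excess |
|---|---|---|---|---|
| 0.10 | 1.0, 0 | 0.06 | 0.342 vs 0.300 | 9% |
| 0.25 | 1.0, 0 | 0.15 | 0.405 vs 0.300 | 31% |
| 0.50 | 1.0, 0 | 0.30 | 0.510 vs 0.300 | 82% |
| 0.10 | 0.8, 0.2 | 0.036 | 0.334 vs 0.308 | 6% |
| 0.25 | 0.8, 0.2 | 0.09 | 0.384 vs 0.321 | 14% |
| 0.50 | 0.8, 0.2 | 0.18 | 0.468 vs 0.342 | 40% |
| any | equal | 0 | equal | 2.5% |

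With a true rate of 50% instead of 30%, the chances for uptake 0.8 and 0.2 fall to about 4%, 9% and 23%.

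**Step 5: mediation.** The indirect effect is the product of the arm-to-mediator path and the mediator-to-outcome path. Corrections add the spurious excess to the first. If they are unrelated to outcome, they also dilute the second. If mDAS had no effect on prescribing, the apparent indirect effect would be the spurious excess times the diluted slope, which is not zero unless the slope is zero. If mDAS does change prescribing, the net error can go either way.

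**The case against.** The strongest reply is that the protocol already has an even-handed source. A review of changes started by clinicians, open to both arms, would separate prescribing from list-keeping, and baseline therapy is recorded for everyone. The wording of the definition also favours a sensible coder: a drug already taken is not a new agent, and a corrected record is not a dose increase. Coding rules of this kind may sit in a statistical analysis plan that is not shown. These points stand in part. They show that the artefact is permitted, not prescribed. They do not remove the problem, because the protocol itself names the reconciled list as the data for medication changes and gives the chart review no precedence.

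A reader might infer that corrections inflate the count in one arm only. The documents do not support that: usual care patients may take up the referral, and mDAS patients may decline the pharmacist and stay in the study with the health coach alone. A reader might also put a firm number on it, such as 110 × 0.60 = 66 mDAS patients with a changed list, and 66 × 0.25 to 66 × 0.50, or about 17 to 33, falsely intensified. That calculation assumes equal allocation, no drop-out, reconciliation of every mDAS patient and an invented share of upward corrections. The discrepancy rate is also not confined to the drug classes in the definition; reconciliation covers supplements and over-the-counter products too.

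The use is limited as well. The mediation analysis is exploratory, runs only if the intervention is effective, and uses a 0.10 criterion to find candidates for later study.

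**Conclusion.** The point holds as a risk of unequal ascertainment. If the text is followed, medication changes and complexity come from a record that mDAS creates after baseline and that Year 1 usual care is not assured of having. Two sources stand side by side without precedence. The error in the arm comparison runs toward mDAS whenever reconciliation uptake is higher there, and it vanishes if uptake is equal.

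The size cannot be fixed from the documents. Over the assumptions shown (q from 10% to 50%; uptake of 80% versus 20%, or 100% versus none) the spurious excess runs from about 0.04 to 0.30 intensifications per patient.

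The scope is narrow: intensification and complexity as process measures, and the exploratory mediation analysis. A reader might extend the concern to the trial's main results, but hemoglobin A1c, blood pressure, LDL-cholesterol, medication adherence and the sample size do not use this list. The change is worth making because it is cheap and the mediator would otherwise be hard to interpret.

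**What to change.** In Section 8.0, item 3, state that in both arms:

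- intensification and regimen complexity are derived from the research-assistant chart review of dated orders initiated by a pharmacist or a physician;
- the comparison is with the same baseline medication record, compiled in the same way for every patient;
- an entry that only corrects the list at reconciliation is not counted as a change.

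Keep the reconciled list as an mDAS process measure, and refer to the chart review wherever Section 12.0 uses intensification.

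Pharmacy fill records, already requested for every participant, should serve only as a sensitivity check. Filling is itself something mDAS aims to change, and Section 2.0 says 20-30% of prescriptions are never filled. An old prescription newly filled because of mDAS would look like a new agent, more often in mDAS.

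The cost is a wording change and some extra abstraction. Changes ordered outside the UI Health record would be missed.

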## **9.0 Data Analysis**

[name] will lead analytic measures in collaboration with [name], IHRP Methodology Research Core. Cost effectiveness analyses will be conducted in collaboration with [name], Loyola University. Sustainability and RE-AIM assessment will involve [name], consultant. Drs. [name] and [name] (Co-PIs) will coordinate all analytic activities with regular meetings and keep data, statistical code, analytic output on a shared drive at IHRP. Additionally [name], along with the co-PIs will coordinate all analytic activities for the sub-study with regular meetings and keep data, statistical code, and analytic output on a shared drive at IHRP.

